### Statistical analysis

#### Data analysis

The Longhua Hospital Shanghai University of Traditional Chinese Medicine will be in charge of data management and statistical analysis in this study. Statistical analysts are not involved in clinical observation; they are responsible for statistical analysis of study data and timely delivery of statistical reports to the study director. Statistical analysis will be performed with SPSS 20.0 software. Measurement data are expressed as mean ± standard deviation. Normality test and homogeneity test of variance will be performed first. In case of normal distribution and homogeneity of variance, a *t*-test is performed, otherwise a non-parametric test is used. Count data are expressed as frequency constituent ratio (percentage) and *X*^*2*^ test is performed. *P* < 0.05 indicates statistical significance.

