### Secondary outcomes

Clinical pulmonary infection score (CPIS): CPIS is a comprehensive clinical and imaging standard to assess the severity of pulmonary infection. It includes the following indicators: body temperature, white blood cell count, tracheal secretions, oxygenation, X-ray pulmonary infiltration, and progress in etiology. The clinical pulmonary infection score is compared before and after treatment. The CPIS details can be found in Additional file 3. Evaluation of disease severity: the scores of patients in the two groups are compared using the APECHA II scoring system before and after treatment. Improvement rate in APECHA II score = (Post-treatment score − Pre-treatment score)/Pre-treatment score. The APECHAII details can be found in Additional file 2. Clearance of drug-resistant pathogens: observed on days 7, 14, 21, and 28.Comparison of mechanical ventilation time and success rate of weaning off the ventilator are calculated if appropriate.Comparison of mortality: mortality is compared on day 28 between the groups.Radiography indicators: pulmonary CT imaging results are compared between the groups before and after treatment.Number of hospitalization days: survival days of patients who die and hospitalization days of those who survive and are discharged.

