### Sample size

Considering that no previous studies have been conducted to calculate the sample size, and assuming that the withdrawal rate is less than 15% [23], we expect that 100 patients will be enrolled in each arm, and that the final sample size of each arm will be at least 85. The data we collect will be helpful to calculate the appropriate sample size in the future and provide reference for further large-scale research.

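### Pre-tests on the outcome data choose between a t-test and an unnamed non-parametric test, yet every continuous outcome is reported as mean ± SD, so for outcomes that fail a pre-test the p-value and the summary answer different questions

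*Protocol article*

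**What the plan says.** The Data analysis section of the protocol article fixes four things for continuous outcomes.

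- Summary: "Measurement data are expressed as mean ± standard deviation". No exception is stated.
- Preliminary step: "Normality test and homogeneity test of variance will be performed first". Neither the tests nor their level are named.
- Choice of test: a t-test if normality and equal variance both hold; "otherwise a non-parametric test is used". The non-parametric test is not named.
- Threshold: a P value below "0.05 indicates statistical significance".

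Count data go to a chi-square test instead.

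The rule governs CPIS, APACHE II (spelled APECHA II in the article), ventilation time and hospital days under Secondary outcomes, and lactic acid, C-reactive protein and procalcitonin under Laboratory tests. Hospital days are defined as "Number of hospitalization days: survival days of patients who die and hospitalization days of those who survive and are discharged".

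**The concern.** The summary is fixed but the test is not. When an outcome fails either pre-test, its p-value comes from a procedure that compares whole distributions (ranks, on the usual reading), while the table shows two means and two SDs. A reader will take a small p-value beside two means as evidence that the means differ.

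Unequal variance alone is enough to trigger the switch. The direct answer to unequal variance is the Welch t-test, which keeps the comparison on means; the rule does not offer it. A rank test is itself sensitive to differences in spread and shape.

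At stake is the reading of the continuous secondary outcomes and of the laboratory markers. The Discussion section relies on several of those markers to explain a possible anti-inflammatory mechanism. The Sample size section also intends the data to help size later research, which makes it useful for the reported means and SDs to belong to the test performed.

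**Working it through.** **Inputs from the document.** The article states that "we expect that 100 patients will be enrolled in each arm" and that "the final sample size of each arm will be at least 85", with withdrawal below 15%. Check: 85 / (1 − 0.15) = 100 per arm, and 5 sites × 40 = 200 in total. Both agree with the text. No effect size, SD or power is given, so there is no power figure to reproduce.

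**Assumptions.** Shapiro-Wilk in each arm and Levene across arms, each at 0.05; Student t-test if all three pass, otherwise Mann-Whitney; two-sided 0.05. The document gives no distributions or variances, so shapes and spreads are assumed and shown as a range. There were 4,000 simulated trials per scenario; the simulation standard error near 5% is √(0.05 × 0.95 / 4000) = 0.0034, about 0.3 percentage points.

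**Results.** The two arms have equal true means in every row. Entries are the percentage of trials declared significant, at 85 / 100 per arm.

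| Scenario | Planned rule | Welch t-test |
|---|---|---|
| Identical normal | 5.9 / 5.1 | 5.7 / 5.1 |
| Identical lognormal | 4.8 / 5.5 | 4.6 / 4.5 |
| Identical exponential | 5.2 / 4.9 | 5.0 / 5.4 |
| Normal, SD 1 v 1.5 | 4.6 / 5.3 | 4.6 / 4.8 |
| Normal, SD 1 v 2 | 5.7 / 5.6 | 4.8 / 4.6 |
| Normal, SD 1 v 3 | 7.3 / 6.6 | 4.8 / 5.2 |
| Lognormal, log-SD 0.5 v 0.6 | 10.1 / 10.8 | 4.8 / 5.3 |
| Gamma, shape 4 v 2 | 14.7 / 16.4 | 5.0 / 5.2 |
| Lognormal, log-SD 0.8 v 1.0 | 24.5 / 27.4 | 5.7 / 4.9 |
| Gamma, shape 2 v 1 | 24.8 / 27.2 | 5.2 / 5.1 |
| Lognormal, log-SD 0.5 v 0.75 | 34.5 / 39.8 | 5.2 / 5.6 |
| Gamma, shape 4 v 1 | 52.9 / 60.0 | 5.6 / 5.3 |
| Lognormal, log-SD 0.8 v 1.2 | 70.2 / 76.7 | 6.2 / 6.7 |
| Lognormal, log-SD 0.5 v 1.0 | 84.5 / 89.7 | 7.4 / 6.5 |

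**How often the rule leaves the t-test.** It did so in 100% of trials in every skewed scenario, in 94% / 96% for normal data with SD 1 v 1.5, and in 100% for SD 1 v 2 and 1 v 3. For identical normal data it did so in about 14%, as expected from three tests at 5%: 1 − 0.95³ = 0.143.

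**The same on the coefficient-of-variation (CV) scale, 85 per arm.** Lognormal CV 0.5 v 0.8: rule about 30%, Welch about 5%. Lognormal CV 0.6 v 1.0: about 41% v 6%. Gamma CV 0.5 v 0.8: about 25% v 5%.

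**What the rank test is detecting.** A lognormal variable with mean 1 has median exp(−s²/2), where s² = ln(1 + CV²). For CV 0.5 v 0.8, s² is 0.223 v 0.495, so the median ratio is exp(0.272 / 2) = 1.15. For CV 0.6 v 1.0, s² is 0.307 v 0.693, and the ratio is exp(0.386 / 2) = 1.21. The means are equal but the medians are not.

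**The case against.** The strongest objection is that these are not false-positive rates. A treatment that does nothing leaves the two arms with identical distributions, and there the rule stays near 5%. In the rows with large percentages the arms truly differ, as the median ratios show, and the rank test is right to say so. This stands. A reader might infer from the table that the plan inflates type I error; the documents and the calculation do not support that.

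Second, a log-scale analysis, a standard choice for skewed markers, also rejects when arithmetic means are equal: about 31% to 32%, 41% to 43% and 46.5% to 48% in the three CV scenarios above. So the comparison with 5% does not show that a rank or log-scale method is wrong. It shows only that neither may be presented as a test of arithmetic means. This also stands, and it shapes the fix.

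Third, where unequal variance is the only problem, the numerical cost is small: about 5% to 7% in the normal rows.

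Fourth, a reader might extend the point to the primary outcome. That outcome is a four-grade category; handled as count data it goes to chi-square and never meets this rule. A reader might also infer that analysts could pick the test to suit the result, but the rule as written is mechanical, and the article keeps the analysts out of clinical observation.

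Finally, a condensed article may leave the name of the test, medians and confidence intervals to a fuller document. Their absence is therefore not the complaint. The complaint is the rule that is stated: a data-driven choice of test beside a single fixed summary.

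**Conclusion.** The mismatch between test and summary follows from the wording of the Data analysis section and needs no simulation. It will affect nearly every skewed or unequal-variance continuous outcome at 85 to 100 per arm. That hospital days, ventilation time, CRP, procalcitonin and lactate are skewed is a reasonable expectation, not something the document states.

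Its size depends on assumptions. Without a spread difference, or with symmetric data, there is little harm (about 5% to 7%). With skew and mild to moderate spread differences, a significant p-value would wrongly suggest a difference in means in about 10% to over 40% of trials with equal means, and in more under the widest spreads tried. Welch stays at 4.5% to 7.4% throughout. The figures also rest on the assumed pre-tests and on reading the unnamed test as Mann-Whitney.

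This is worth correcting, but it is confined to secondary and laboratory measures provided the graded primary outcome is analysed by chi-square.

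**What to change.** Delete the pre-test sentence and name one method per continuous outcome in advance, matched to its summary.

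- **CPIS and APACHE II**, both measured before and after treatment: a baseline-adjusted difference in means with a 95% CI and robust standard errors, or a Welch comparison if no adjustment is made.
- **CRP, procalcitonin, lactate and day counts:** choose one of two routes for each. Either the Welch t-test on means, reported as mean ± SD with the mean difference and CI; or a named log-scale or rank analysis, reported with geometric means or medians and the matching effect (a ratio of geometric means, or a shift estimate) with its CI. State that the second route is not to be read as a difference in arithmetic means.
- **Summary sentence:** limit mean ± SD to outcomes analysed on means.

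The cost is a few lines of wording. No new data are needed, and SPSS 20.0, the software named in the article, already prints the unequal-variance t-test. The choices should be recorded before outcomes are compared by arm, since otherwise they would again depend on the data.

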### Primary outcome

#### Efficacy evaluation criteria in TCM

Evaluation criteria by clinical manifestations are in reference to the *Criteria of Diagnosis and Therapeutic Effect of Diseases and Syndromes in Traditional Chinese Medicine* (Chinese Medicine Industry Standards of the People’s Republic of China; ZY/T001.1–94):
Clinical control: After treatment, symptoms and signs almost disappear and patients return to normal activities and work. The efficacy rate for syndromes is ≥ 90%.Excellent efficacy: After treatment, symptoms and signs and the results of examinations improve significantly. The efficacy rate for syndromes is ≥ 60% but < 90%.Efficacy: After treatment, symptoms and signs and the results of examinations improve. The efficacy rate for syndromes is ≥ 30% but < 60%.Lack of efficacy: After treatment, symptoms and signs and the results of examinations do not improve compared to before treatment. The efficacy rate for syndromes is < 30%.

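### The four-grade primary outcome is tested with an unadjusted chi-square although baseline APACHE II and CPIS are measured; the test is valid, but gives up some power if baseline severity is prognostic

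*Protocol article*

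**What the plan says.** The primary outcome (Efficacy evaluation criteria in TCM) is a four-level grade. Each level carries a verbal description and a band of a syndrome efficacy rate, with cuts at 30%, 60% and 90%. For the top grade the article says "The efficacy rate for syndromes is ≥ 90" per cent, and for the bottom grade "The efficacy rate for syndromes is < 30" per cent. No formula for the rate is printed, and no syndrome score is named. The explicit reference to the pre-treatment state is in the bottom grade, where findings "do not improve compared to before treatment".

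Under Data analysis, "Count data are expressed as frequency constituent ratio (percentage") is followed by a chi-square rule: "test is performed. *P* < 0.05 indicates statistical significance". Measurement data are treated in the same unadjusted way: "In case of normal distribution and homogeneity of variance, a *t*-test is performed, otherwise a non-parametric test is used". No covariate, stratum or regression model is named.

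Baseline severity is nevertheless recorded. Under Secondary outcomes, "the scores of patients in the two groups are compared using the APECHA II scoring system before and after treatment" (the article's spelling of APACHE II), and CPIS is likewise compared before and after treatment. Randomization and allocation describes 1:1 assignment with 40 patients per site and does not mention stratifying by severity.

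**The concern.** Patients come from emergency departments and ICUs and are aged 40 to 85, so severity at entry plausibly varies widely and may well predict the grade reached after treatment. The trial measures that severity with two scores and does not use either in the stated primary test.

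Two things are at stake, both conditional on severity being prognostic. First, a test that ignores a prognostic covariate has less power than one that conditions on it. Second, if the arms happen to differ in severity, the reported comparison cannot be read as holding severity equal. If a covariate is then chosen after the imbalance has been seen, the choice is open to challenge; naming it beforehand avoids this.

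**Working it through.** **The plan's own figures.** Sample size expects 100 per arm with withdrawal below 15%: 100 × (1 − 0.15) = 85 evaluable per arm. Five sites × 40 = 200 patients. Both reproduce. The article states no effect size, response rate or power, so there is no power figure to reproduce and every power below rests on assumptions.

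**Chance imbalance.** With n per arm, the standardised difference in baseline means has SD √(2/n).
- n = 85: √(2/85) = 0.153. P(|d| > 0.2) = 2 × [1 − Φ(0.2/0.153)] = 2 × [1 − Φ(1.30)] = 19%. P(|d| > 0.3) = 2 × [1 − Φ(1.96)] = 5%.
- n = 100: √(2/100) = 0.141, giving 16% and 3%.

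These apply to any one covariate.

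**Power, by simulation.** Inputs: 85 per arm (Sample size); two-sided 5% level (Data analysis; the two sides are assumed). Assumed: control grades from worst to best of 30/30/25/15%; a logistic latent variable; a treatment effect of 0.9 on that scale, kept constant after standardisation by using 0.9/√(1 − R²); and a share R² of latent variance explained by baseline of 0, 10, 20 or 30%. There were 2,000 trials per scenario, so the standard error of one power figure is about √(0.67 × 0.33/2000) = 1.1 points.

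The first three power columns concern the grade reduced to effective versus not effective, analysed by plain chi-square or by logistic regression with the baseline covariate.

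| R² | Chi-square, unadjusted | Logistic, adjusted | Gain (points) | Type I error of chi-square: two-level / four-grade |
|---|---|---|---|---|
| 0% | 67.5% | 66.2% | −1.3 (none) | 4.2% / 4.9% |
| 10% | 67.7% | 69.3% | 1.6 | 5.1% / 4.8% |
| 20% | 66.5% | 69.5% | 3.0 | 4.9% / 5.0% |
| 30% | 66.1% | 74.1% | 8.0 | 4.9% / 4.8% |

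The unadjusted test holds its error rate throughout. The gain from adjustment runs from nothing to about 8 points.

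**Keeping a second effect apart.** In the same simulation, the four-grade chi-square had 74–77% power and an unadjusted rank-sum test on the four grades 87–90%, a difference of about 11–14 points. That loss comes from ignoring the order of the grades and is not part of this point. A proportional-odds model would recover it as well, but it should not be credited to baseline adjustment.

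**The case against.** **An article leaves covariates to the full protocol or SAP.** Silence about covariates would indeed be no finding, and the article does not rule out an adjusted analysis. It does choose a test for count data, however, and that test covers the primary outcome. The point is made against that stated choice.

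**The test is valid.** This stands. A reader might infer that a chance imbalance passes into the primary result as bias. It does not: randomisation makes such imbalance part of the variation that the 5% error rate already covers, and the simulated type I error agrees. The issue is efficiency and interpretation.

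**The grade may already be scaled to baseline.** A reader might take it as fact that the grade is a banded percentage change from a baseline syndrome score. The article does not say so. It refers to an outside standard, prints no formula and names no score. The grade is apparently judged against the state before treatment, and no more can be said. If that reading is right, the outcome takes some account of baseline by construction, though the test still does not condition on it. The APACHE II and CPIS part of the point does not depend on this.

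**The gain may be negligible.** This stands in part. A separate simulation assumed that the grade is a percentage reduction cut at 30/60/90% and that baseline and post-treatment scores correlate at 0.5. Adding the baseline syndrome score to a linear model of the grade gave 85% and 82% power (two settings of outcome spread), against 85% and 80% for an unadjusted ordered test: a gain of 0 to 2 points. No simulation used APACHE II or CPIS data, and the table above adjusts a two-level grade, so it is only a guide to what a proportional-odds model would gain.

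**Larger gains might seem available** from analysing a post-treatment syndrome score directly, or from applying the linear-model variance formula. Neither is supported here. The article defines no such score, patients who die before the end of treatment would have none, and the formula does not carry over to an ordinal model of four grades.

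**Conclusion.** The point holds as a modest, conditional improvement in efficiency. The only stated test for the primary grade ignores two severity scores that the trial records before treatment. If those scores are prognostic, prespecified adjustment would gain some power: about 0 to 8 points under the assumed grade frequencies, effect size and 0–30% explained variance. It would also deal with chance imbalance, for which each covariate has about a 19% chance of exceeding 0.2 SD at 85 per arm. If they are not prognostic, nothing is gained. How prognostic they are cannot be learned from the article. The stated chi-square is neither invalid nor biased.

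**What to change.** In Data analysis, name as the primary analysis a proportional-odds regression of the four-grade outcome on treatment, with baseline APACHE II and baseline CPIS as prespecified covariates. If a baseline syndrome score is recorded, define it and add it. Keep the table of the four grades by arm, with percentages, as description.

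APACHE II and CPIS are already scored before treatment, so the change is to analysis wording only; whether a baseline syndrome score exists must be confirmed first. There are two costs. The result is an adjusted odds ratio, which clinical readers will find less familiar than a difference in percentages. The proportional-odds assumption must also be checked and reported.

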### Randomization and allocation

In each study site, patients with MDRO HAP that fulfill the inclusion criteria and do not meet any of the exclusion criteria are assigned to the trial group or control group according to the corresponding random numbers extracted in the order at visit. Each study site will enroll 40 patients for a total of 200 over the five study sites. A random number table generated using Statistical Analysis Software (SAS), version 9.2, using the randomization method, will be used to assign the participants in a ratio of 1:1, with 100 patients each in the trial group and control group. A researcher will generate the allocation sequence and enroll participants and the clinical researchers will assign participants to interventions. The clinical researchers at each center will provide packaged drugs to the participants according to the randomization number on the packaging; the code labeling will conform to the principles of GCP. The statistician will uncover the blinding as necessary.

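### The primary outcome is a four-level ordered grade, but the only test stated for categorical data is a chi-square test, which ignores the order and, for a roughly proportional shift, gives up about 10 to 17 points of power at odds ratios of 1.5 to 2.5

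*Protocol article*

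**What the plan says.** Under Primary outcome, Efficacy evaluation criteria in TCM, the protocol article defines four grades cut at 90%, 60% and 30% of a syndrome efficacy rate. The second-best begins "Excellent efficacy: After treatment, symptoms and signs and the results of examinations improve significantly" and the worst begins "Lack of efficacy: After treatment, symptoms and signs and the results of examinations do not improve compared to before treatment". The grades are plainly ordered.

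Under Statistical analysis, Data analysis, there are two rules. Continuous measurements get a t-test if normality and equal variance hold; "otherwise a non-parametric test is used". For categorical data, "Count data are expressed as frequency constituent ratio (percentage) and" a chi-square test is performed. The threshold is P "< 0.05 indicates statistical significance", with no statement of sidedness. No test is assigned to the primary outcome by name, and no trend, rank or ordinal method is mentioned.

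Under Randomization and allocation, assignment is described by site: "In each study site, patients with MDRO HAP that fulfill the inclusion criteria" and avoid the exclusions receive random numbers in order of visit, and "Each study site will enroll 40 patients for a total of 200 over the five study sites". The words stratified and blocked do not appear.

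Under Sample size, 100 patients per arm are to be enrolled, with at least 85 expected to remain after withdrawals below 15%. No effect size, grade distribution or power is given.

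**The concern.** A Pearson chi-square test on a 2x4 table has 3 degrees of freedom and gives the same P value if the grade labels are shuffled. It asks whether the two distributions differ in any way. The trial asks whether adding the decoction moves patients towards better grades. A significant result could therefore arise without either arm being better overall, and the test supplies no single measure of benefit.

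The stated test also spreads its sensitivity over patterns that are not of interest. Recruitment is fixed at 200 and was not derived from a power calculation, so the choice of test is one of the few ways left to gain precision at no cost in patients.

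**Working it through.** **The article's own figure.** 100 x (1 - 0.15) = 85 evaluable per arm, and 5 x 40 = 200 enrolled. Both reproduce. There is no stated power to reproduce.

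**General comparison.** At two-sided 5%, the critical values are 3.841 (1 df) and 7.815 (3 df). A 1-df ordered test has 80% power at non-centrality 7.85. A 3-df test at the same non-centrality has 64.5% power. To reach 80% it needs 10.90, and 10.90 / 7.85 = 1.39, that is about 39% more patients.

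**Worked example (assumed inputs).** Control distribution, best to worst, 10/25/35/30%; common odds ratio 2.0; 85 per arm; no site differences.
- Control cumulative proportions from the best grade: 0.10, 0.35, 0.70. Odds: 0.111, 0.538, 2.333.
- Doubled odds: 0.222, 1.077, 4.667. Treated cumulative proportions: 0.182, 0.519, 0.824.
- Treated distribution: 18.2/33.7/30.5/17.6%.
- Chi-square non-centrality = 85 x sum of (p1 - p2)^2 / (p1 + p2) = 85 x (0.02375 + 0.01281 + 0.00309 + 0.03203) = 85 x 0.07168 = 6.09.
- Power of the 3-df chi-square at 6.09: 52.5%.
- A rank test has almost the same non-centrality (6.09) on 1 df: power 69.4%.
- Collapsed to effective versus lack of efficacy (0.300 v 0.176, mean 0.238): 85 x 0.1235^2 / (2 x 0.238 x 0.762) = 3.57 on 1 df, power 47%.

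**Range.** Simulation with 10,000 trials per scenario, 85 per arm, five equal sites, proportional odds, and four assumed control distributions (worst to best: 25/25/25/25, 35/35/20/10, 20/40/30/10, 50/25/15/10), with no site differences:

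| Common OR | Chi-square, 3 df | Site-stratified rank test |
|---|---|---|
| 1.5 | 19-21% | 30-31% |
| 2.0 | 53-54% | 69-71% |
| 2.2 | 64-66% | 79-81% |
| 2.5 | 78-79% | 90-91% |
| 3.0 | 92% | 97% |

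At 100 per arm and OR 2.0 the figures are 59-61% and 76-77%. The collapsed two-grade chi-square at 85 per arm and OR 2.0 ranges over 36-60%, always below the ordered test.

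**Site on its own.** This compares unstratified with site-stratified rank tests at OR 2.0 and 85 per arm, with an assumed between-site SD on the log-odds scale. The stratified test gains nothing at SD 0, about 3 points at SD 0.5, about 6 at SD 0.8 (63% v 69%) and 11-12 at SD 1.0.

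**Type I error.** With no treatment effect and site SD 1.0, the unstratified chi-square rejects in 3.3-3.7% of trials and the stratified rank test in about 5%. Ignoring site makes the test conservative.

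**When the ordered test loses.** Take control 30/35/25/10% and treated 30/20/25/25% (worst to best). The cumulative odds ratios are (0.70/0.30)/(0.70/0.30) = 1.0, (0.50/0.50)/(0.35/0.65) = 1.86 and (0.25/0.75)/(0.10/0.90) = 3.0, far from proportional. The chi-square non-centrality is 85 x (0.15^2/0.55 + 0.15^2/0.35) = 85 x 0.1052 = 8.94, power 71%. The rank test has about 39%.

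**The case against.** The Data analysis section is a generic paragraph in a condensed article. It never mentions a 2x4 table, does not tie a test to the primary outcome, and a fuller analysis plan may exist. For site adjustment this objection stands: its absence is silence, and a full plan could supply it. A reader might infer that the article states an unstratified analysis of a stratified design. It says neither, so site is offered here as an inexpensive improvement and not as an error. For the ordering the objection does not stand. The article does state its rule for categorical data, and that is the only stated rule that covers a graded outcome; the non-parametric option is attached to continuous measurements that fail their checks.

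The gain rests on a roughly proportional shift. This stands: the last calculation above reverses the ranking, and the documents give no basis for predicting the pattern of effect.

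The loss is one of efficiency. This also stands. No power was promised, so none is missed, and the direction of any difference would be visible in the reported percentages, though the test itself would not establish it.

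A reader might call the chi-square the least efficient choice available. It is not: in the worked example the collapsed two-grade test is weaker still. A reader might also combine order and site into a single large loss, such as 45% v 69% at SD 0.8. About 6 of those 24 points are due to site; the rest is the ordering loss.

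**Conclusion.** The point holds as a recommended change. The endpoint is ordered, the only stated categorical test is not, and at 85 per arm the cost is about 17 points of power at a common odds ratio of 2.0, about 10 to 17 points over 1.5 to 2.5, and about 5 at 3. This assumes two-sided 5%, a roughly proportional shift and the control distributions shown. Stratifying by site adds between nothing and about 12 points for between-site SDs of 0 to 1.0, which are assumed.

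The documents do not support a claim that the planned test is invalid or that its type I error is inflated.

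The grade definitions raise a separate question, which the power figures neither support nor need. Lack of efficacy pairs no improvement with a rate below 30%, so a patient improved by 20% meets one half only and is too low for the next grade. Clinical control pairs a rate of at least 90% with "symptoms and signs almost disappear and patients return to normal activities and work", so a patient at 95% who is still in hospital fits no grade. A reader might infer that these gaps will be filled by unblinded judgement in favour of one arm. The article does not establish that: no placebo is described, yet it refers to coded packaging and to unblinding, and the cited standard is not available.

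**What to change.** In the Data analysis section, name the primary analysis: a proportional-odds model for the four grades with treatment and site as factors, or the van Elteren or row-mean-score Cochran-Mantel-Haenszel test stratified by site. Report a common odds ratio with its 95% CI; where a stratified rank test is chosen, take the odds ratio from the model. Keep the grade percentages by arm and the chi-square test as a secondary display, which also shows whether any effect is uneven across the grades.

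Separately, reconcile the verbal and percentage rules under Efficacy evaluation criteria in TCM so that every patient falls into exactly one grade.

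The cost is wording: no extra patients, visits or data, and SPSS 20 fits ordinal regression. The drawbacks are an effect measure less familiar to readers than a percentage, and reliance on a roughly ordered, proportional shift. Both changes should be made before outcome data are analysed.
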